## Abstract

**Introduction:**

The use of nicotine products among youth is increasing, while existing cessation services remain underutilized. Thus, the U-Niko intervention has been developed to provide an evidence-based, youth-oriented approach for effective nicotine cessation.

**Methods:**

This protocol describes a two-arm cluster randomized controlled trial of youth aged 16–25 in 55 municipalities in Denmark. Prior to the study a stratified randomization was carried out using the online randomization program Sealed Envelope, allocating 27 municipalities to the U-Niko intervention group and 28 municipalities to the control group (tobacco and nicotine cessation recruitment and counseling as usual). The primary outcomes will measure the effectiveness of all three focus areas in the intervention group compared to the control group: A) the municipal counselors’ self-efficacy in youth cessation counseling, B) the number of recruited youths for cessation counseling, and C) the self-reported 14-day point prevalence of abstinence of youth at six months follow-up. Secondary outcomes are the number of recruited youths in a municipality compared to the previous year, continuous abstinence, and validated 14-day point prevalence of abstinence at six-months follow-up.

**Discussion:**

By evaluating all three focus areas of the U-Niko intervention, this study aims to provide robust evidence for improving youth cessation interventions at local and national levels.

**Trial registration:**

The study was registered in ANZCTR (ACTRN12624001470583) on 18/12/2024. The Universal Trial Number is U1111-13-14-6117.

## Introduction

In recent years, youth nicotine use has risen significantly, with nearly 36% of Danish youth (15–29 years) using at least one tobacco or nicotine product [1]. While more than half of young people who smoke and more than 70% of those who use oral nicotine products wish to quit [1], many struggle with high levels of nicotine dependence, making unassisted quitting difficult [2].

The detrimental effects of smoking extend beyond physical health, adversely affecting mental health and contributing to increased school absence among youths [3–5]. Furthermore, early exposure to nicotine in any form may yield long-term negative consequences for brain development [6–8] and has been found to function as a “gateway drug” to other psychoactive substances, including cocaine and cannabis [9–11].

Although Denmark offers cost-free, high-quality smoking cessation services, young people underutilize these services and have lower quit rates than adults [12]. Group-based smoking cessation counseling is the most frequently used and is very effective [13]; however, municipal counselors report limited experiences with youth-oriented quit services [12] and call for evidence-based strategies to better support young users.

Despite this growing need, there is a lack of high-quality studies on youth tobacco and nicotine cessation interventions, and the existing literature is inconclusive [14]. However, interventions based on social cognitive theory [15] and group-based smoking cessation counseling [16] seem to be effective in promoting longer-term abstinence in young adults. Regarding the cessation of nicotine products (not cigarettes): Low-grade evidence suggests that multi-component interventions that include counseling and peer elements and a text-based cessation program based on behavioral support may be effective in the cessation of nicotine products in youth. Pharmacotherapy seems to be well tolerated by young people, but no significant effect has been shown [17,18].

Given the rising use of nicotine products among youth, their difficulties in quitting unassisted, and the underutilization of existing cessation services, there is a pressing need for effective, evidence-based interventions tailored to young users.

This paper describes the study protocol for a cluster randomized trial evaluating the effectiveness of the U-Niko intervention (‘Unge uden nikotin’ – Youth without nicotine), a tailored tobacco and nicotine cessation intervention for youth. Developed for Danish municipalities, which are key stakeholders responsible for cessation efforts, the intervention aims to provide evidence for improving youth tobacco and nicotine cessation strategies.

## Methods

### Study design

This study is a cluster randomized controlled trial (RCT) including 55 Danish municipalities and aimed at youth aged 16–25. The intervention period will run from January 1, 2025, to December 31, 2025. The municipalities were randomly allocated to either the U-Niko intervention group or the control group in the spring of 2024. The youth participants will receive either the U-Niko intervention or a control condition (municipal cessation activities as usual, described under the section *Intervention*) based on the municipality in which they live, go to school, work, or, in some other way, have their daily activities. “Cessation activities” are defined as counselling processes over several sessions, not brief advice.

The study is a field trial in which all intervention activities are performed by municipalities, not researchers. The intervention municipalities will not receive any economic or manpower support from the research group.

Recruitment and cessation counseling will be conducted via the municipalities and will occur during the entire intervention year from January 1, 2025, to December 31, 2025. Enrollment and follow-up assessments will be conducted via the municipalities in cooperation with the national database on tobacco and nicotine cessation (STOPbasen) and the research group. STOPbasen is a Danish database where most cessation activities in Denmark are routinely registered and have high validity. Data collection is estimated to be complete in June 2026, with results expected to be ready to publish approximately 6–12 months later (Fig 1).

**Fig 1 pone.0323514.g001:**
[figure not shown]
Time schedule of enrolment, interventions, and assessments on participant outcome inspired by the SPIRIT 2013 reporting guidelines.

The study is conducted by the Center for Clinical Research and Prevention, Frederiksberg University Hospital, following the General Data Protection Regulation (GDPR) (EU) 2016/679, and was registered in ANZCTR on December 18^th^, 2024 (ACTRN12624001470583). The Universal Trial Number (UTN) is U1111-1314–6117. The Regional Health Research Ethics Committees in the Capital Region of Denmark waived the need for ethical approval of the project (no. F-24044815).

All youth receiving support to quit tobacco and/or nicotine products in the intervention and control municipalities will complete a short baseline survey at their first contact with the cessation activities, which will entail a written consent form for the study. The Danish Data Protection Authority and Danish Patient Safety Authority do not require parental permission for minors aged 15 years or older.

### Inclusion criteria

All Danish municipalities were invited to participate in the study. However, municipalities that participated in the development and feasibility study (n = 3) were excluded from the invitation to participate in the effect evaluation.

Eligible youth participants for the tobacco and nicotine cessation courses are youths aged 16 to 25 years who are currently (daily or occasionally) using at least one tobacco or nicotine product and wish for assistance to quit. Participants will be *excluded* from the study if they do not meet the listed inclusion criteria or fail to provide contact information and informed consent during enrolment and baseline assessment.

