#### B. Recruitment.

The recruitment strategy is developed as a step-by-step guidance on where to recruit and how to contact youth arenas for recruitment (i.e., schools, workplaces, fitness centers, sports clubs, campuses, barracks, and meeting places for youth), as well as how to encourage them to cooperate. The intervention group will receive free recruitment materials (videos and letters) and guidance on how to recruit in different youth arenas over time.

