#### C. Cessation.

At the first cessation session, all participants in both the intervention and control municipalities will complete a baseline questionnaire on contact information, personal characteristics, information on tobacco and/or nicotine use, and the U-Niko score. The baseline questionnaire also contains a consent form for participation in the study. The baseline questionnaire will be registered in STOPbasen.

Further, the young participants in the intervention group will be invited to answer a short online survey on their experiences with the intervention after the course has ended (4 weeks post-target quit date), regardless of their tobacco and nicotine status.

Six months after the targeted quit date, all participants (in both the intervention and control groups) will be contacted by phone to examine the long-term effects of the cessation offer. A research assistant will contact the participants multiple times by phone and send text messages to decrease the number of missing values at follow-up.

All participants will be informed that each completed questionnaire (baseline survey, post-intervention survey (only intervention group), and six-month follow-up survey) will be entered into a raffle with the chance to win a gift certificate worth 1000 DKK (~134 euros/139 USD). In total, six participants from the intervention municipalities and four from the control municipalities will be drawn to win.

Participants who report being tobacco- and nicotine-free at the six-month follow-up will be invited to undergo a saliva cotinine test to validate their abstinence. The saliva test will be mailed to each participant who has agreed to participate and will be conducted via an online interview using Teams. The participant will take the test and show the answer to the research staff during the online meeting, discard the test, and receive a gift certificate for 300 DKK (~40 euros/42 USD), regardless of the outcome of the validation test.

The primary outcome is *the effect of the cessation course,* which will be measured using *long-term self-reported PPA* (not using any tobacco or nicotine product in the last 14 days) six months after the targeted quit date in the intervention municipalities compared with the control municipalities. To assess this, participants will be asked, “Have you used any tobacco or nicotine products in the last 14 days?” (Yes/No).

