### Additional measures

Additional measures of the participants will be assessed in the baseline survey, including demographic information such as age, sex, gender, socioeconomic status, U-Niko dependence score, and product use (type, frequency, and duration). Furthermore, data on the employment of youth participants at baseline will be obtained from the Danish Education Register.

Additional measures for youth cessation counselors will be assessed during the post-intervention municipal follow-up survey. These measures include education and previous experience with tobacco and nicotine cessation activities.

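### Occasional users can count as successes on the 14-day primary outcome without changing their use; outcome C should be adjusted for baseline frequency and backed by an analysis of at-least-weekly users

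*Protocol article*

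**What the plan says.** Under Inclusion criteria, the protocol article makes eligible those aged 16 to 25 who are "currently (daily or occasionally) using at least one tobacco or nicotine product and wish for assistance to quit". It does not say what occasional means and does not ask for use within any period before entry. Participants are excluded only "if they do not meet the listed inclusion criteria or fail to provide contact information and informed consent during enrolment and baseline assessment".

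Under Measures and data assessment, C. Cessation, the primary outcome is defined as "not using any tobacco or nicotine product in the last 14 days) six months after the targeted quit date". It is taken from one yes/no item, "Have you used any tobacco or nicotine products in the last 14 days", with no reference to the participant's use at baseline.

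The Data analysis plan for outcome C is an intention-to-treat GLMM with non-respondents counted as users. It states no restriction, stratification or subgroup by baseline frequency. It mentions a final adjusted model without listing its covariates. The Additional measures section shows that the baseline survey records "U-Niko dependence score, and product use (type, frequency, and duration". Continuous abstinence from the target quit date is a secondary outcome.

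Recruitment follows randomization and differs by arm. Municipalities were allocated in spring 2024 and youths are recruited during 2025. U-Niko municipalities receive guidance on "where to recruit and how to contact youth arenas for recruitment", while control municipalities recruit as usual.

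**The concern.** A 14-day abstinence endpoint shows that someone has stopped only if that person would otherwise have used within 14 days. For a participant who uses about once a month, a negative answer at six months may simply reflect the usual pattern.

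Two things are at stake. First, participants who would be scored as successes whatever they receive carry no information about the course, so they shrink the contrast and cost power. Second, because the way youths are found is itself part of the intervention, randomizing municipalities does not guarantee the same mix of light and heavy users in the two arms. A difference in mix would then appear in outcome C as a difference between courses, although the article wants the contribution of each focus area assessed separately.

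**Working it through.** **1. The plan's own figure.** Inputs from Sample size calculations: 23% versus 34%, ICC 0.05, 20% loss, 27.8 youths in each of 55 municipalities. Two-sided 5% significance and 80% power are assumed, since the article states no power.

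- Per arm: (1.96 + 0.8416)² × (0.23×0.77 + 0.34×0.66) / 0.11² = 7.849 × 0.4015 / 0.0121 = 260.4, so 261.
- Design effect: 1 + (27.8 − 1) × 0.05 = 2.34.
- Total: 2 × 261 × 2.34 / 0.80 = 1,527, against 1,526 stated.

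The sample size reproduces and is not in question. It serves as the baseline for step 3.

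**2. How often an unchanged occasional user is scored abstinent.** Assume use occasions fall at random, on average every d days. The chance of a clean 14-day window is exp(−14/d). Multiply by 0.80, because the plan expects 20% loss and counts non-respondents as users (the same loss is assumed for this group).

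| Average use | Clean window | Scored abstinent |
|---|---|---|
| Weekly (d = 7) | 13.5% | 10.8% |
| Fortnightly (d = 14) | 36.8% | 29.4% |
| Monthly (d = 30) | 62.7% | 50.2% |
| Every two months (d = 60) | 79.2% | 63.4% |

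For fortnightly or rarer use, a range of about 30% to 63% is reasonable.

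**3. Equal shares: dilution.** Let a share f in both arms be scored as successes whatever the treatment, with 23% and 34% holding for the rest. Arm rate = f + (1 − f) × 0.23 or 0.34. Effective number per arm = 1,526 × 0.80 / (2 × 2.34) = 260.9. Power is from the pooled-variance two-proportion formula.

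| f | Control | U-Niko | Odds ratio | Power |
|---|---|---|---|---|
| 0 | 23.0% | 34.0% | 1.73 | 80% |
| 5% | 26.9% | 37.3% | 1.62 | 73% |
| 10% | 30.7% | 40.6% | 1.54 | 66% |

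**4. Unequal shares: bias.** Suppose the course has no effect. Let s be the share of infrequent users in an arm and p the probability that one of them is scored abstinent, with 23% for everyone else. Arm rate = s × p + (1 − s) × 0.23, so the spurious difference is (difference in s) × (p − 0.23).

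- 10% versus 5%: 0.05 × (0.30 − 0.23) = 0.35 points (about 0.4), up to 0.05 × (0.63 − 0.23) = 2.0 points.
- 20% versus 10%: 0.10 × 0.07 = 0.7 points, up to 0.10 × 0.40 = 4.0 points.

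The sign reverses if the control arm has more infrequent users. The article gives 23% for all control participants. If that already averages over some infrequent users, the rate in the rest is lower and these differences are somewhat larger.

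**5. What adjustment does.** In step 4 the arms are identical within each frequency group, so a model that includes baseline frequency removes that difference. It does not remove the dilution in step 3; only an analysis restricted to more frequent users does that.

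**The case against.** The strongest reply is that this matters little in practice. Entrants must be current users who want help, cessation activities are multi-session counselling, and the U-Niko course asks for seven meetings and a commitment to stop all products. Few once-a-month users may come forward. This stands as a limit on size, because the article gives no share, but it does not close the gap between the two definitions.

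Next, continuous abstinence would not count a continuing occasional user as a success, so a discordant result would be visible. That is right, but it is a secondary outcome and nothing links it to the reading of the primary one. Validated abstinence helps less, since it tests only those who already report abstinence and agree to the test.

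Third, the final adjusted model may already include frequency, and an article may leave its covariates to the full plan. That stands too: the absent list is not the fault. The fault is the pairing of the stated eligibility with the stated endpoint.

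A reader might go further and infer that adjustment cannot help. For imbalance it can, as step 5 shows. A reader might also infer that recruiting in youth arenas will favour U-Niko. The article does not describe where control municipalities recruit or how often recruits in either arm use, so the direction is unknown.

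**Conclusion.** The mismatch is real on the stated text: an unchanged, less-than-fortnightly user can be scored a success on primary outcome C. Strictly, it is the 14-day criterion that such a person may satisfy at entry, since the endpoint itself is scored only at six months.

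The size is unknown and rests on assumptions: the shares, random timing of use, 20% loss in this group, and 23% for everyone else. Within these, equal shares of 5% to 10% always scored as successes reduce power to about 73% to 66%. Unequal shares bias the difference by about 0.4 to 4.0 points either way in the scenarios shown, against the planned 11.

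Larger figures are tempting. If 80% of infrequent users were scored abstinent and the shares were 20% versus 5%, the formula would give 0.15 × 0.57 = 8.6 points. With 20% non-response counted as use, 80% would require every responding infrequent user to be abstinent, and nothing in the article supports so wide a gap in shares. The documents do not show that the primary result will be spurious. They show that it could not, alone, be read as cessation. That merits an inexpensive improvement to the analysis plan, not a redesign.

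**What to change.** - Keep all enrolled participants as the primary intention-to-treat set. Replacing it with a subset of youths recruited after randomization would change the primary population of a registered trial and would still leave differences in mix among weekly and daily users.
- Include baseline frequency of use as a covariate in the outcome C GLMM. It is already in the baseline survey. Say how a missing value is handled, because the plan otherwise provides for listwise deletion.
- Pre-specify, as the key supporting analysis, the same GLMM restricted to participants who use daily or at least weekly at baseline. Weekly is a sensible cut, since step 2 gives an unchanged weekly user only about an 11% chance of being scored abstinent.
- Report both odds ratios with 95% confidence intervals. Interpret a primary result as a cessation effect only alongside the restricted estimate and continuous abstinence.
- Show baseline frequency by arm in the baseline table, so that any difference in mix can be seen.

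The cost is plan wording, settled before outcome data are analysed, and a smaller, less precise supporting set. No new data are needed, and outcome B keeps all recruits.

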### Randomization

All municipalities in Denmark that did not participate in the feasibility study (N = 95) were invited to register for the trial in March 2024. Of these, 55 municipalities (58%) accepted and were randomized into either an intervention or a control group using the online tool Sealed Envelope (Fig 2). Randomization was stratified by municipality size and inter-municipal cooperation (health clusters affiliation) to minimize the potential spill-over effect. Randomization was blinded to the researchers conducting the allocation. Participating municipalities differed from non-participants in several ways. Non-participating municipalities tended to be smaller (population < 50.000) and characterized by a higher average disposable income in 2024. In contrast, participating municipalities more frequently received funding from the Danish Health Authorities for tobacco and nicotine prevention and reported more cessation activities, including experiences with youths, in 2023. However, both groups had similar proportion of youth in the target group at the time of the invitation to participate. For a detailed comparison, see S1 Table in the Supporting Information.

**Fig 2 pone.0323514.g002:**
[figure not shown]
Overview of the intervention enrolment, preparation, trial activities, and data assessment.

### Sample size calculations

The sample size calculations are based on the expected difference in self-reported point prevalence abstinence (PPA) six months after the targeted quit between the intervention and control groups. Based on data from STOPbasen and international literature [14,19], the abstinence rate under the intention-to-treat analysis (ITT) approach is estimated to be 23% in the control municipalities and 34% in the intervention municipalities. The power calculations incorporate an intraclass correlation coefficient (ICC) of 0.05 to account for expected similarities among participants within clusters. This adjustment reflects the likelihood that young people within the same municipality receive support from the same youth coach/cessation counselor and are exposed to the same contextual environment (e.g., schools or other youth arenas). Despite extensive follow-up procedures, a 20% loss to follow-up is expected and is included in the sample size estimation [20]. Based on these assumptions, each municipality must include at least 27.8 youth participants in cessation activities during the entire intervention year, a total of 1,526 youth participants.

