#### C. Cessation.

The analyses of the primary outcome on self-reported 14-days PPA at six months follow-up will follow the intention-to-treat (ITT) principle, assuming that all non-respondents are currently smoking or using nicotine. Data will be analyzed using a generalized linear mixed model (GLMM) to account for clustering, recognizing that youth participants within the same municipality may be more similar to each other than to participants from other municipalities. Results will be presented in a table as odds ratios (ORs) for 14-day PPA at six months after the targeted quit date, with corresponding 95% CIs. A p-value < 0.05 will be considered statistically significant.

Secondary outcomes, including short-term self-reported abstinence, continuous self-reported abstinence, and validated 14-days PPA at six months follow-up, will be analyzed using the same GLMM approach as for the primary outcome and presented in tables as ORs with corresponding 95% CIs. In addition, a table will present and compare the baseline characteristics of all youth participants between the intervention and control groups, including age, educational level, type of nicotine product used, and follow-up participation rates.

Given the high degree of data completeness in STOPbasenwe intend to employ a complete case analysis, excluding patients with any missing values in the included variables from the analysis (listwise deletion). Consequently, a sensitivity analysis using an as-observed approach will be conducted, including only participants with a valid follow-up. Sensitivity analyses will be performed using the final adjusted model from the main analyses. This approach builds on the assumption that data is Missing Completely At Random (MCAR). However, when it comes to smoking status, data are more likely to be Missing Not At Random (MNAR). Therefore, if necessary, considering the number of missing values and loss to follow-up, a sensitivity analysis using a chained multiple imputation model will be conducted based on the final adjusted model in the main analyses.

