Because the study is a field trial and the intervention occurs in a real-life setting, there are also some uncertainties regarding the comparison groups, data registration, and follow-up [29]. The youth-oriented cessation activities in the municipalities have been very sparse in the last few years, and there is a risk that only a few young persons will be included in 2025, resulting in too low a power to detect significant differences between the intervention and control municipalities. However, in early 2024, the Danish Health Authorities launched a call in which municipalities interested in improving their work with youth tobacco and nicotine cessation activities could apply for funding. In total, 58 million DKK (~7,7 million euros) were allocated to this work and funding must be used between fall 2024 and 2027. This may have a negative impact on the study, as some municipalities will have a much higher activity level than anticipated. Nonetheless, both the intervention (~44%, n = 12/27) and control municipalities (~54%, n = 15/28) received funding, and therefore, the hopefully positive effect of the increased resources will be present in both the intervention and control groups. Therefore, it should be feasible that the calculated sample size requirements on 27.8 participants during the whole intervention year in each municipality can be accommodated. The analysis of the effectiveness of the U-Niko intervention (recruitment and cessation) will consider that some of the municipalities (more control municipalities) have received extra funding and, therefore, have more resources.

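### The sample size adds 20% for loss to follow-up to abstinence rates that already count lost participants as users, so 27.8 per municipality (1,526 in total) does not match the planned primary analysis

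*Protocol article*

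**What the plan says.** Protocol article, Sample size calculations: "the abstinence rate under the intention-to-treat analysis (ITT) approach is estimated to be 23% in the control municipalities and 34% in the intervention municipalities". An ICC of 0.05 is used. The paragraph then states that "a 20% loss to follow-up is expected and is included in the sample size estimation" and concludes that "each municipality must include at least 27.8 youth participants in cessation activities during the entire intervention year", 1,526 in total. Target power is not given.

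Protocol article, Data analysis plan, C. Cessation: the primary analysis of 14-day abstinence at six months "will follow the intention-to-treat (ITT) principle, assuming that all non-respondents are currently smoking or using nicotine". The significance level is p < 0.05. The same section also mentions a complete case analysis with listwise deletion and an as-observed sensitivity analysis.

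Protocol article, Discussion: the figure of 27.8 per municipality is repeated as the requirement, and is judged feasible because municipalities in both arms received extra funding. The Discussion also warns that few inclusions could leave power too low, and that "some municipalities will have a much higher activity level than anticipated".

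**The concern.** An allowance for loss is needed when lost participants leave the analysis and reduce its size. Here they do not: a non-respondent is scored as a user and stays in the denominator. The cost of loss falls on the rates, which are lower than they would be among respondents, and the 23% and 34% are presented as rates of exactly that kind. Dividing by 0.8 as well charges the trial a second time for the same loss.

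What is at stake is how the trial's size is read. The Discussion uses 27.8 per municipality as the benchmark for feasibility and for the risk of low power. If enrolment ended at, say, 1,000 to 1,200, the trial would seem to have missed its requirement, although at equal municipality sizes and 80% power it would have met the one that follows from the article's own assumptions.

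**Working it through.** **Inputs from the article.** Rates 0.23 and 0.34; ICC 0.05; loss 20%; 27 and 28 municipalities, taken as k = 27.5 per arm; p < 0.05.

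**Assumed, because not stated.** Two-sided test, 80% power, equal municipality sizes.

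**Step 1: individually randomized size per arm.**
n = (1.96 + 0.8416)² × (0.23 × 0.77 + 0.34 × 0.66) / 0.11² = 7.849 × 0.4015 / 0.0121 = 260.4, rounded up to 261.

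**Step 2: reproduce the published figure, with the inflation.**
- At 27.75 per municipality (1,526 / 55), the design effect is 1 + 26.75 × 0.05 = 2.3375. Then 261 × 2.3375 / 0.8 = 762.6, so 763 per arm and 1,526 in total.
- Solving for the cluster size instead, m = n(1 − ICC) / (k − n × ICC). With n = 261 / 0.8 = 326.25, m = 309.94 / 11.1875 = 27.70, total 1,524. With the unrounded n (325.55), m = 27.56, total 1,516.

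The figure is recovered to within about 1%. The route is not unique. At 85% power n is 298; with the design effect at the analysed size, m = 283.1 / 12.6 = 22.47, and dividing by 0.8 gives 28.1 per municipality and about 1,544 in total. Both routes contain the division by 0.8.

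**Step 3: the same inputs without the inflation (80% power).**
m = 261 × 0.95 / (27.5 − 13.05) = 247.95 / 14.45 = 17.16, total 944. With the unrounded n, m = 17.09, total 940. The published total is about 1.6 times this (1,526 / 944 = 1.62).

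**Step 4: power of 1,526 analysed as planned.**
Effective size per arm = 27.5 × 27.75 / 2.3375 = 326. Then 0.11 × √(326.4 / 0.4015) − 1.96 = 3.136 − 1.96 = 1.176, which is 88% power.

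**Step 5: would dropping the losses make the calculation consistent?**
If 20% are lost in each arm and are then left out, the rates among respondents that match 23% and 34% are 0.23 / 0.8 = 28.8% and 0.34 / 0.8 = 42.5%. The article uses 23% and 34%, so its rates and its allowance for loss belong to different analyses under either reading.

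**Step 6: unequal municipality sizes (secondary).** The article gives no coefficient of variation (CV) of recruitment, so a range is assumed. Two methods, both for 1,526 analysed in full (mean 27.75 per municipality):
- Standard unequal-cluster design effect, 1 + ((1 + CV²) × 27.75 − 1) × 0.05.
- Mixed-model weighting, effective size per arm 27.5 × E[m / (1 + (m − 1) × 0.05)], with gamma-distributed sizes m.

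| CV | Standard design effect | Mixed-model weighting |
|---|---|---|
| 0 | 88% | 88% |
| 0.6 | 81% | 85% |
| 0.8 | 76% | 83% |
| 1.0 | 70% | 80% |

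**The case against.** The strongest reply is that the inflation does no harm: it raises power, the municipalities were randomized in spring 2024, recruitment is fixed to calendar year 2025, and no decision is triggered by 1,526. That stands, and it limits the point to a correction of a stated figure.

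A second reply is that the analysis plan also names a complete case analysis, so some loss from the analysed set is foreseen. That is true, but it does not rescue the calculation, because complete-case rates would then be required (Step 5).

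Three stronger readings are tempting, and the documents do not support them:
- *The trial is underpowered.* The double counting works the other way. Power below 80% at 1,526 arises only under assumed size variation, and at which CV depends on the method.
- *The design effect was wrongly taken at the enrolled rather than the analysed size.* Power is not stated, and the 85% route with the analysed size comes within about 1.2% of 1,526. Which route was used cannot be told.
- *Ignoring unequal sizes makes the figure too small.* The text sets a minimum for each municipality. If all 55 reach it, variation above it cannot take power below plan. Equal sizes are an inference from one common figure, and a condensed article may leave the allowance for size variation to the full protocol.

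**Conclusion.** The point holds. The rates and the handling of non-respondents, both fixed in the article, already carry the loss, so the further 20% counts it twice. This conclusion needs no assumption about power.

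Its size does. At two-sided 5%, 80% power, ICC 0.05 and equal sizes, the requirement is about 17 per municipality (940 to 944 in total) rather than 27.8 (1,526), and 1,526 gives about 88% power. The error is conservative.

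Variation in municipality size is secondary but relevant if the target is met only on average. Randomization was stratified on municipality size, and municipalities are free to choose how many courses they run. The figures in Step 6 are illustrations under assumed CVs and should not be read as fixed values.

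**What to change.** 1. In Sample size calculations, state the target power and that the test is two-sided, if that is so.
2. Remove the 20% inflation for the primary analysis that counts non-respondents as users. If losses are instead to be dropped, keep an allowance for loss but base the calculation on complete-case rates (about 28.8% and 42.5% if 20% are lost in each arm).
3. Restate the per-municipality and total requirement, and change the matching sentence in the Discussion.
4. Report power at the restated total, and at 1,526 if that is kept as the enrolment aim, over an assumed range of recruitment CV, and name the method. At 1,526 this is about 81 to 85% at CV 0.6, 76 to 83% at CV 0.8 and 70 to 80% at CV 1.0.

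The cost is rewording one paragraph and one sentence, plus a short calculation. Recruitment, design and analysis are unchanged.
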